## Abstract

Protecting infants’ vulnerable brain during repeated painful procedures like blood-sampling and immunizations in early life is a top priority in neonatal health care. Use of parent-delivered pain management may safeguard the infant brain but at the brain level, it is still unclear what drives the analgesic effect of parent-led interventions such as skin-to-skin contact, breastfeeding, and the parent’s live singing. The objective of this study is to advance our understanding of the neural mechanisms behind parent-led pain management in newborn pain care. Twenty mother-infant dyads will be studied during a planned blood sampling venepuncture, with skin-to-skin contact, breastfeeding, and the mother’s live singing. The potential interbrain synchronous cerebral activation in cortical regions of interest will be registered using functional Near-Infrared Spectroscopy (fNIRS) hyperscanning. Secondly, registration of skin conductance, heart rate variability, and the mother’s gaze will be registered. Social and musical interactions will be studied using microanalysis, as will pain using the Behavioral Indicators of Infant Pain (BIIP). The Swedish Research Ethical Review Authority has approved the study (Dnr 2025-02283-01).

## Introduction

Today, we know that infants, including prematurely born infants, feel, experience and have a sensory memory of pain and that they are more vulnerable to the negative effects of pain than older children and adults [1–3]. Modern neuroimaging techniques combined with quantification of painful events show a clear positive correlation between higher neonatal pain exposure and functional and structural deviations in the growing brain [4,5]. It is also shown that a higher number of invasive procedures is associated with more sensory processing problems and altered hypothalamic-pituitary adrenal (HPA) axis function, which can be harmful for the infant’s developing nervous system and can divert energy from crucial brain development, at least up to school age, especially in girls [6,7]. In contrast, reducing pain in early life leads to more optimal brain growth and neurodevelopment [8].

Goksan and colleagues showed using functional Magnetic Resonance Imaging (fMRI) that infants can process and interpret pain in a manner similar to adults, and that almost all regions of the brain that are activated during acute pain in adults are also activated in healthy full-term newborn infants [1,9,10]. This suggests that infants have the capacity to experience the affective dynamics of pain in the same way as adults [1]. The same group has also shown using fMRI that the descending pain modulatory system is fully functional at birth in term-born healthy infants, similar to that observed in adults [9]. This may suggest that in the term newborn infant, brain regions involved in descending pain modulation may influence the dampening, alteration, and alleviation of pain experience, as well as the modification of pain behaviour.

The neural mechanisms underlying emotion and social cognition as well as early sensory and recorded music processing in infants, have previously been investigated using functional Near-Infrared Spectroscopy (fNIRS) [11]. In one fNIRS study, preterm infants repeatedly listened to recorded Western art music, and the results showed significant hemodynamic changes in the left superior temporal gyrus in response to variations in the recorded music (timbre, dynamics, and rhythm). The authors concluded that infants’ auditory cortex demonstrate functional maturity in processing multiple dimensions of recorded musical input and the results support the evidence of synchronous large-scale brain networks involved in musical perception [12]. fNIRS studies investigating newborn infants’ brain responses to maternal speech, showed that infants are highly responsive to their mother’s emotional prosody with significantly enhanced functional connectivity within the bilateral frontotemporal network, as well as increased neural activity in the right superior temporal gyrus during the mother’s affectively expressive speech, especially positively charged mother-infant emotional interactions [11,13]. In previous studies, fNIRS has demonstrated that tactile stimulation, especially through skin-to-skin contact, significantly activates the frontal, somatosensory, and motor cortices in preterm neonates supporting emotional regulation [14]. It is reasonable to deduce that infants from birth and at brain level are responsive to their psychobiologically attuned parents’ multimodal and multisensory visual-facial, auditory-prosodic, and tactile-gestural nonverbal pain-alleviating interventions, especially positively valenced nonverbal communications, such as the parent’s live infant-directed singing [15], skin-to-skin contact [16], and breastfeeding [17].

### Synchrony for pain alleviation

Synchrony is described as a complex social coupling process of two or more individuals in the here-and-now, and interbrain synchrony refers to an alignment of brains between two individuals [13]. Early stressful ruptures of the infant-parent emotional attachment bond that are not routinely followed by repair interactions, occurring, for example, during painful procedures poorly alleviated and performed without the parent’s protective comfort and love, will cause disturbances in the synchronization of the dyad’s interpersonal psychobiological systems [13]. Lack of synchrony with the parent is stressful for the infant, and stress may exacerbate a painful experience. In a stressful and painful situation, such as the blood sampling procedure, the infant seeks proximity to the parent, not just physical closeness but an emotional mind-body proximity where a right brain-to-right brain nonverbal communication is shared between the infant’s and parent’s minds [13]. The empathic psychobiologically attuned parent will intuitively, nonverbally, and interactively regulate her infant through social biofeedback maximizing positive and minimizing negative affect to maintain interbrain synchrony in the dyad. Right-lateralized interbrain synchronization, i.e., a synchronization between the right temporoparietal cortex of the infant brain and the right temporoparietal cortex of the parent’s brain, is embedded in the parent-infant biopsychosocial interplay associated with synchronous multisensory stimulation [13]. Shared positive affects specifically activate the parent’s and her infant’s right temporoparietal junction, known as the central node of the social brain, involved in regulation between and within brains, minds, and bodies [13]. Since this region of interest, the right temporoparietal junction and surrounding temporoparietal cortex, sits on the cortical surface, it is accessible to fNIRS and hyperscanning techniques.

Stress, which is a dominant element in pain, is defined as “an asynchrony in an interactional sequence” [13]. When a period of stress is followed by a repair period of synchrony, this provides regulation and recovery in the parent-infant dyad. Emotion regulation is key for pain alleviation [18,19]. The dyad’s nonverbal reciprocal moment-to-moment right brain-to-right brain emotional protocommunications of face, prosody, and gestures, will enhance synchronization followed by mutual regulation of the dyad’s emotional states which will give the infant and the parent a sense of pleasure and vitality [13]. Regulation occurs when the mother-infant dyad is synchronized on all levels from neural activity to physiological states, such as heartbeat rhythm, to pupil size, to behavioural facial expressions, reciprocal vocalisations and body postures [13]. It is theorized that synchrony consists of biopsychosocial reciprocal processes, including co-regulation present in a mother-infant nonverbal protocommunication where both individuals adjust their social attention, and accelerate their arousal to each other [13].

Using hyperscanning with functional Near-Infrared Spectroscopy (fNIRS) [20] will enhance our understanding of the multimodal and multisensory biopsychosocial parent-led pain alleviating methods. Hyperscanning illuminates the social interaction between two nonverbally communicating brains [13]. In this hyperscanning study, based on previous research, we deduce that parent-led pain alleviating interventions, with bidirectional visual-facial (mutual gaze), auditory-prosodic (live parental singing), and tactile-gestural (affectionate touch, skin-to-skin contact and breastfeeding) nonverbal communications, will activate interbrain synchrony in the dyad helping the infant reach and maintain homeostasis and a state of regulation before, during and after the painful procedure. The proto-musical elements of parental infant-directed singing are ideal for arousal regulation and affect coordination as well as for affect sharing between parent and infant, and the parent’s live singing provides a contingent responsivity and continuum in the regulation of the infant’s arousal systems [18]. Hence, positively charged interbrain synchronization has the capacity to dissolve a negative painful affective spiral.

In moments of interpersonal synchrony, previous research shows that maternal live infant-directed vocalizations as well as skin-to-skin contact promote stabilization of physiological and behavioural parameters regulating the infant’s autonomic nervous system, heart rate, and respiratory rate [21].

Heart rate variability (HRV) is a non-invasive measure of cardiac autonomic control giving information on the sympathetic and vagal modulations evoked by pain [22]. In newborn infants HRV is considered an indicator of the maturity of the autonomic nervous system [23]. During the first week of life, both total, low-frequency (LF), and high-frequency (HF) HRV following acute pain showed inconsistent results among full-term infants. The LF/HF ratio decreased in response to acute pain and was the only consistent measure [24]. An increase in skin conductance (SC) reflects the infant’s arousal intensity and level of stress in response to a painful procedure. Skin-conductance, also named Galvanic Skin Response (GSR) or Electrodermal activity (EDA), is a measure of the sympathetic nervous system’s response to stress and pain [25,26]. An increase in the number of SC peaks per second, as well as the area under small peaks and the area under large peaks, indicates a higher stress level.

Mutual gaze is essential for the interbrain synchrony in the right temporoparietal cortex which responds to visual, auditory, and tactile stimuli [13]. Adult gaze serves as a pivotal social cue in early development, with infants demonstrating marked sensitivity to its presence and directional orientation [27]. In a study of vaccination of 2-month-old babies, it was found that the mother-to-infant gaze increased if the mothers sang live to their infants [28]. The infant’s facial actions, especially movements in the mouth area, are thought to be important behavioural responses to pain, helping infants to communicate their affective state with their caregivers. Recent studies on neonatal pain assessment have used eye-tracking device to evaluate where the observer looks during pain assessment of the infant [29–32]. In one study, when adults with and without a health care profession assessed pain in infants from looking at pictures of infants’ faces, the health care professionals more often correctly identified the infants’ pain by looking repeatedly and longer at the nasolabial furrow feature in the faces [29]. A similar study design was used comparing the correlation of visual tracking between health and non-health professionals when observing newborn infants’ face images at rest and during a painful procedure [31]. Health care professionals focused more on the infants’ mouths and the nasolabial furrows and had fewer visual fixations on the infants’ eyes compared to non-health professionals [31]. Silva and colleagues [30,32], investigated health care professionals’ gaze when in the first study assessing pain from images of newborn infants at rest and during a painful procedure and, in the second study, when assessing newborn infants pain expressions during a live heel puncture procedure. In the first study, the paediatricians’ gaze fixations were greater in the infants’ mouth and forehead than in the nasolabial furrow [32]. Results from the second study showed that most paediatricians focused their visual attention on the infant’s face, especially on the lower face, than on the infant’s hands [30]. Little is known, however, about how parents look at their infants while interacting with them during a painful situation. Social mutual gaze is just one attribute through which the psychobiologically attuned mother perceives and resonates with the infant’s pain experience.

### Parents alleviate infants’ pain responses

It is crucial for an infant in a painful situation, as well as for forthcoming painful experiences, that her/his parent is emotionally available, attuned to the infant’s state, and attuned to moment-to-moment changes of the infant’s affects, capable of noticing signals and able to regulate and share the infant’s states before and during the pain experience [18]. However, it is not yet established which brain processes are involved in parent-led pain management and which brain functions are coupled and synchronous in the parent and infant brain when a parent sings in combination with skin-to-skin contact and breastfeeding during a painful procedure.

In an ongoing music therapy study, in a non-painful context, fNIRS is used to investigate the synchronization of cerebral activation between the infant and the parent, as well as between the infant and the music therapist while she sings lullabies accompanied by a vibro-acoustic monochord during parent-infant skin-to-skin contact [33,34]. In a randomized controlled study, using fMRI, the infant-directed live singing performed by a music therapist had beneficial effects on very preterm infants’ brain network connectivity in cognitive, socio-emotional, and motor functions [35]. Prior research has emphasized the importance of including parental vocalizations in neonatal pain management, showcasing its ability to improve the infant’s physiological stability, emotional regulation, and attachment to carers including mitigating the infant’s pain responses and decreasing parents’ anxiety [36].

The interaction between mothers and their infants in a painful context [37,38] has previously been studied with fNIRS and hyperscanning [20,39]. Bembich et al. showed synchronized cortical activation between the mother and her newborn infant while the mother, without holding the infant, observed heel prick blood sampling on her infant [40].

To our knowledge, no previous research has used fNIRS and hyperscanning to explore interbrain synchrony in infants and their mothers during parent-led multisensory and multimodal pain alleviation. It is important to develop evidence-based in-depth knowledge to better inform neonatal care on how and why combined parent-led pain management should be promoted and implemented. This will increase parents’ possibilities to protect their infant’s brain from pain during the many painful procedures early in a child’s life.

Protecting infants’ vulnerable brain during repeated painful procedures like blood-sampling and immunizations in early life is a top priority in neonatal health care. Parents are, and should be, a fundamental resource in infant pain management, for both healthy and hospitalized infants [41,42]. With interbrain synchronized regulation in the mother-infant dyad, the use of parent-delivered pain management may safeguard the infant brain during a painful procedure but, at the brain level it is still unclear what drives the analgesic effect of parent-led interventions.

## Materials and methods

The overall objective of this project is to advance our understanding of the neural mechanisms behind parent-led pain management in newborn pain care. Understanding at the brain level the mechanisms that modulate the effects of parental interactions with skin-to-skin contact, breastfeeding, and parents’ live singing on pain perception in neonates, could also provide insight into pain learning and protective actions against repeated pain exposure for the parent-infant dyad.

### Hypotheses

Changes in oxygenated haemoglobin (Oxy-Hb) and deoxygenated haemoglobin (Deoxy-Hb) in the prefrontal, posterior frontal, parietal and temporal areas in both hemispheres of the brain in mothers and infants will be synchronously activated, during an intervention with skin-to-skin contact, breastfeeding, and parent’s live singing during venepuncture for blood sampling.Corresponding synchrony will be seen in heart rate variability and skin conductance activity.The neurophysiological responses are correlated to the infant’s pain reaction, parent’s gaze, and social and musical interactions.

### Sample, setting and procedure

#### Study participants*.*

Twenty mothers and their healthy newborn infants will be recruited among birthing mothers in Örebro county, Sweden. Inclusion criteria: healthy mothers above 18 years of age, able to understand Swedish or English language, having had a vaginal delivery; infants with gestational age above 37 + 0, birth weight above 2 500 g, and Apgar score at 1 minute above 7. Exclusion criteria: infants who received analgesics or sedatives within 24 hours before the blood sampling, or who failed at the newborn hearing screening test. The number of mother-infant dyads was motivated from previous studies using fNIRS during heelstick (Bembich 2022: 16 dyads [40]; Bembich 2018: 20 dyads in each group [43]), and from the above-mentioned ongoing music therapy study in Switzerland [33,34]. The sample size was determined using a Minimum Effect Size of Interest (MESI) analysis (G-Power 3−1, Heinrich Heine University, Düsseldorf, Germany) [44]. Effect size 0.35, alpha 0.05, beta 0.80, 7 repeated measurements, revealed a sample size of 11 dyads. To compensate for attrition, we will recruit 20 dyads and the pilot test with two dyads indicates that both recruitment and the recording procedures are feasible and easily tolerated by the mother and the infant. The initial recordings will help in optimising all recordings to get an analysable sample of at least 11 dyads. The mother and infant will be studied during the ordinary blood sampling for metabolic screening, done by venepuncture, i.e., no extra pain will be inflicted.

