#### Statistical analyses.

The primary hypothesis, interbrain neural synchrony, will be analysed using General Linear Mixed Models (GLMM) and WTC [20] for both Oxy-Hb and Deoxy-Hb. After preprocessing of the signals, an interpersonal comparison will be performed for each region of interest and each time point, within each dyad. The false discovery rate (FDR) will be set to 0.05.

For the secondary outcomes, SC and HRV, synchrony will be analysed at the time points within each dyad before calculating means or medians on the group level. All statistical analyses will be done using parametric statistics (means, standard deviations, t-test or ANOVA) for data that are normally distributed and non-parametric statistics (median, inter-quartile range, Mann-Whitney or Kruskall-Wallis) for data that are not normally distributed. Chi-square test will be used to compare group distributions.

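### The 11-dyad figure prints power as beta and fits one omnibus test at alpha 0.05, so 80% power is not shown for the FDR-controlled primary family

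*Protocol article*

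**What the plan says.** Under *Study participants*, the protocol article reports a G*Power calculation for a minimum effect size of interest: "Effect size 0.35, alpha 0.05, beta 0.80, 7 repeated measurements, revealed a sample size of 11 dyads". Twenty dyads are to be recruited to cover attrition, and the aim is an analysable sample of no fewer than 11. Earlier fNIRS studies, with 16 dyads and with 20 per group, are cited in support of the number.

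Under *Statistical analyses*, the primary hypothesis (interbrain synchrony) is to be analysed with mixed models and wavelet transform coherence for both Oxy-Hb and Deoxy-Hb. Mother and infant are compared in every region of interest at every time point. Multiplicity is handled in one sentence: "The false discovery rate (FDR) will be set to 0.05".

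Under *Hypotheses*, the first hypothesis is broad: "prefrontal, posterior frontal, parietal and temporal areas in both hemispheres of the brain in mothers and infants will be synchronously activated". The introduction (*Synchrony for pain alleviation*) gives special weight to one region, the right temporoparietal junction, "known as the central node of the social brain".

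The sample-size paragraph mentions neither regions, chromophores nor the FDR.

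**The concern.** There are two problems. First, the printed input "alpha 0.05, beta 0.80" does not lead to the printed result, because a type II error of 0.80 means power of 0.20. Second, the calculation and the primary analysis are both in the article and describe different things. One is a single test at alpha 0.05 that pools seven measurements. The other is a family of tests by region, chromophore and time point under FDR control.

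The stake is how a null result will be read. Eleven analysable dyads is the working target, which tolerates a loss of 9 of 20 (45%), and the *Limitations* section names data attrition as a pitfall. If the study ends near 11, a negative finding would carry an 80% power claim that was never worked out for the analysis that produced it.

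**Working it through.** **Inputs from the article.** Effect size 0.35, alpha 0.05, seven measurements, 11 dyads required, 20 recruited; two chromophores; four areas in two hemispheres; FDR 0.05.

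**Assumptions.** The article does not state the effect metric, the within-dyad correlation ρ or the nonsphericity factor ε. I read 0.35 as Cohen's f and vary ρ and ε. I take 4 × 2 = 8 regions and 8 × 2 = 16 outcomes, treated as independent.

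**Formula** (one-group within-factor repeated-measures ANOVA, m = 7): λ = f²·N·m·ε/(1−ρ), df1 = (m−1)ε, df2 = (N−1)(m−1)ε. Power is the noncentral F tail beyond the critical value.

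**Reproducing 11.** At N = 11, f²·N·m = 0.1225 × 11 × 7 = 9.4325.

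| ρ, ε | λ at N = 11 | Power at 10 | Power at 11 | Smallest N for 0.80 |
|---|---|---|---|---|
| 0.4, 1 | 9.4325/0.6 = 15.72 | 0.768 | 0.818 | 11 |
| 0.5, 0.75 | 9.4325 × 0.75/0.5 = 14.15 | 0.758 | 0.809 | 11 |
| 0.7, 0.4 | 9.4325 × 0.4/0.3 = 12.58 | 0.781 | 0.828 | 11 |
| 0.5, 1 | 9.4325/0.5 = 18.87 | 0.851 | 0.892 | 10 |

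The pairs (0.6, 0.6) and (0.8, 0.25) also give exactly 11. So 11 is reproduced as one omnibus test at alpha 0.05 with power 0.80. With power 0.20, as printed, the answer is 3 dyads (ρ 0.5, ε 1) or 4 (the other settings). Other variants do not fit: the Cohen effect-size option gives 17, the SPSS option 21 and the multivariate test 16.

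**The planned family at 11 dyads.** One omnibus test for each of the 16 outcomes is the generous reading, since tests at each time point would make 16 × 7 = 112. If a single outcome is non-null, the relevant level is about 0.05/16 = 0.0031. With more true effects, Benjamini–Hochberg power was simulated (simulation error about 0.01).

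| ρ, ε | One non-null (0.05/16) | 4 of 16 | 8 of 16 | All 16 | 20 dyads at 0.05/16 |
|---|---|---|---|---|---|
| 0.4, 1 | 0.44 | 0.58 | 0.68 | 0.79 | 0.89 |
| 0.5, 0.75 | 0.42 | 0.56 | 0.66 | 0.78 | 0.87 |
| 0.7, 0.4 | 0.42 | 0.56 | 0.68 | 0.80 | 0.86 |
| 0.5, 1 | 0.57 | 0.72 | 0.81 | 0.88 | 0.95 |

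The pairs (0.6, 0.6) and (0.8, 0.25) give 0.41–0.45 in the first power column and 0.81–0.82 in the all-16 column.

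**Single time-point contrasts.** Seven measurements add no power to a test at one time point. Converting f = 0.35 to a standardised paired difference gives 0.65 to 1.31, depending on the pattern of means and on ρ (0.4 or 0.5). Power at 11 dyads is then 0.49–0.97 unadjusted and 0.03–0.34 at the strictest FDR step, 0.05/112.

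**The case against.** Several replies have force.

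*The recruited number is 20, not 11.* This is true, and with all 20 usable the omnibus tests hold up well (0.86–0.95 at 0.05/16 in the settings tabulated). But the article sets its floor at 11 and attaches the power claim to that number.

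*FDR control is adaptive, and the hypothesis posits effects everywhere.* This also stands. At ρ 0.5 and ε 1, power reaches 0.80 once about half the outcomes are real. A reader might infer that no test in the family has 80% power, or that the stated power is definitely not delivered. The documents do not support that; the shortfall depends on ρ, ε and the share of true effects.

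*Sphericity.* A reader might infer that the calculation assumed sphericity. It cannot be told: 11 arises with ε from 0.25 to 1, given a suitable ρ. Sensitivity runs both ways. At ε 0.5, power at 11 is 0.67 with ρ 0.5 but 0.89 with ρ 0.7, so no single pair should be presented as the true power. Leaving ρ and ε out of an article is not a fault in itself; they matter here because the figure cannot be placed without them.

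*All 16 at once.* The first hypothesis could be read as requiring detection in every region and chromophore. Nothing in the analysis text makes success depend on that, and a joint probability would rest on independence of Oxy-Hb and Deoxy-Hb from the same channels.

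*Change over time versus synchrony above chance.* An omnibus F over time points tests change, which may not be what the first hypothesis asserts. But the synchrony analysis follows a cited method not available here, which may supply a chance reference, so I do not press this.

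**Conclusion.** The point holds as a mislabel plus a mismatch. Beta 0.80 should be power 0.80, and the 11 dyads belong to one omnibus test at unadjusted alpha 0.05, not to the family of comparisons named as primary. For three settings that give exactly 11, power at 11 dyads in a 16-outcome family is about 0.42–0.44 with one true effect, 0.56–0.68 with a quarter to a half, and 0.78–0.80 with all. At ρ 0.5 and ε 1 the range is 0.57–0.88. These figures rest on Cohen's f, eight regions, independence and the ρ and ε shown, none of which the article states. What is established is that 80% power at 11 dyads is not shown for the primary analysis. That the study of 20 is underpowered is not established.

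**What to change.** 1. Write power 0.80 (beta 0.20).
2. State that the 11-dyad figure is for one omnibus repeated-measures test at alpha 0.05, and give the effect metric, ρ and ε that were entered.
3. Then do one of two things. Either restate power at 11 and at 20 dyads for the FDR-controlled family, as a range over the share of true effects. Or prespecify one primary region, chromophore and contrast, with the rest secondary under FDR 0.05. The right temporoparietal junction is a natural candidate given the introduction, but the choice is the investigators'.
4. Say that all usable dyads among the 20 will be analysed, and stop treating 11 as the threshold of adequacy.

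The cost is a paragraph of text and a less favourable stated figure at 11; under the second option, the other regions also become secondary. No further dyads are needed. Recruitment is scheduled to start in spring 2026, and any primary test should be fixed before data are seen.
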